### Recruitment

Initial recruitment of psychotherapists started in July 2020 and is expected to be finished in July 2021, supported by MEDIVERBUND AG as well as the collaborating professional associations MEDI Baden-Wuerttemberg e.V., Freie Liste der Psychotherapeuten and Deutsche Psychotherapeutenvereinigung (DPtV). First patient in is expected to be included in January 2021. Psychotherapists taking part in the PNP contract were contacted via e-mail and invited to one of four online information events. Furthermore, psychotherapists can express their study interest at www.psychonlinetherapie.de. After informed consent has been given and inclusion and exclusion criteria confirmed, eligible psychotherapists complete baseline assessment. Psychotherapy outpatient practices are consecutively randomized to one of the three trial arms. Psychotherapists are subsequently invited to a 1-day training, which will be tailored to the respective trial arm (PSYCHOnlineTHERAPY_fix/flex_; CBT_standard_). MEDIVERBUND AG assigns a practice structural feature for billing project-specific blended therapy services in accordance with the PNP contract.

Once psychotherapists are allocated to one of the three trial arms and trained for intervention and study protocol adherence, patient recruitment starts. This is expected to take place from January 2021 until June 2022. The psychotherapists assess if patients are potentially eligible for the trial. If this is the case, patients are informed by their psychotherapists about the possibility to take part in PSYCHOnlineTHERAPY. Interested patients will give their informed consent and schedule an appointment for the telephone-based clinical interview online on a tablet provided for study purposes only in the psychotherapy practice. Patients are then invited for the online baseline assessment and the baseline clinical interview is conducted. Once the baseline assessments have been completed, patients enter the trial and are treated for their condition according to trial arm allocation of their psychotherapist following the intervention rational as described below. Follow up assessments will take place as outlined in the flow chart (Figure 1).

**Figure 1 F1:**
[figure not shown]
Flow chart.

### Randomization, Allocation, and Masking

Psychotherapist outpatient practices will be consecutively randomly allocated to (a) PSYCHOnlineTHERAPY_fix_, (b) PSYCHOnlineTHERAPY_flex_, or (c) CBT_standard_ and informed about group membership via e-mail. Randomization will take place at a psychotherapist practices level. That means, therapists in joint practices are randomized jointly into one of the three trial arms to avoid trial arm contamination. Randomization will be conducted by an independent researcher who is blind regarding the study conditions. Whereas, blinding of psychotherapists is not possible, data collectors are blinded regarding treatment condition. Treatment condition is only known by the study personnel administering allocated treatments to psychotherapy practices. Randomization will be stratified by the number of therapists per practice (single therapist vs. more than one therapist). Two randomization lists will be generated by using the web-based programme Sealed Envelope (www.sealedenvelope.com). Randomization will happen on an individual level and an allocation ratio of 1:1:1 will be performed. In case of dropouts and if it becomes apparent that more than 75 therapists are needed to reach the sample size of *N* = 900 patients, additional therapists will be randomized.

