### Participants and Procedure

#### Cluster Definition

The trial will be conducted in psychotherapy outpatient practices in South-West Germany (Baden-Wuerttemberg) that take part in the PNP (Psychotherapy, Neurology, Psychosomatic, and Psychiatry) selective health care services contract of the health insurance companies AOK Baden-Wuerttemberg and Bosch BKK, managed by MEDIVERBUND AG according to §73c SGB V. This contract defines (amongst others) specific psychotherapy services for patients as outlined below. Clusters are defined by psychotherapy outpatient practices that are run by licensed psychotherapists who are PNP contract partners (i.e., authorized to bill according to the PNP contract; https://www.mediverbund-ag.de/file/4922). Psychotherapists who are not PNP contract partners themselves may participate in the study, if they are employed in a practice owned by a PNP contract partner. More than one therapist per practice is allowed to participate in the study.

Psychotherapists are eligible for inclusion in case of a given informed consent and if they (a) are actively working as a psychological psychotherapist, a medical specialist for psychiatry and psychotherapy or psychosomatic medicine and psychotherapy, another physician working as psychotherapist, or a children and adolescent psychotherapist, (b) are (employed in a practice owned by) a PNP contract partner, (c) hold a CBT license, (d) are available during recruitment and assessment period (self-report regarding no already known time-offs), and (e) are capable of including 12 patients into the study during the recruitment period (18 months; self-report). Enrolment and opening of clusters will take place over the entire recruitment period in order to reach the recruitment target of 900 patients. The recruitment target is a median of 12 patients per participating psychotherapist in order to achieve recruitment of 900 patients.

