### Sample Size and Power Calculation

The sample size calculation is based on a random intercept model comparing the primary outcome (PHQ-ADS at T3) between treatment conditions while accounting for the nested structure of the data. Although this model is simpler than the target statistical analyses for the primary outcome presented below, it allows to avoid speculative assumptions about numerous unknown model parameters. The focal hypothesis is that both intervention groups PSYCHOnlineTHERAPY_fix/flex_ are not inferior to CBT_standard_ (= non-inferiority trial). Non-inferiority is assumed if the confidence interval (CI) of the standardized mean comparissson between PSYCHOnlineTHERAPY_fix/flex_ is completely above SMD = −0.24, which is considered as a lower threshold of clinical significance (49). We assume one-sided tests with α = 0.025 (Bonferroni-adjusted) and 1-ß = 0.8, an intra-cluster correlation coefficient (ICC) of 0.01 with a median cluster size of 12 eligible patients as feasible number to be recruited within the recruitment period. Based on these assumptions, the present trial aims at a sample size of 25 psychotherapy outpatient practice clusters and *n* = 300 patients per study arm with an allocation ratio of 1:1:1 (PSYCHOnlineTHERAPY_fix_, PSYCHOnlineTHERAPY_flex_, CBT_standard_; for formulas see (50).

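### The protocol names two incompatible units of randomisation, the practice and the individual, and counts clusters in therapists in one place and in practices in another

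*Protocol article*

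**What the plan says.** All references are to the protocol article.

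**Unit of randomisation.** Randomization, Allocation, and Masking opens with the practice: "Randomization will take place at a psychotherapist practices level". It adds that "therapists in joint practices are randomized jointly into one of the three trial arms to avoid trial arm contamination". Stratification is also a practice characteristic: "Randomization will be stratified by the number of therapists per practice (single therapist vs. more than one therapist". Two sentences later the unit changes, without qualification: "Randomization will happen on an individual level and an allocation ratio of 1:1:1 will be performed".

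**Enlarging the trial.** The next sentence deals with dropouts and slow recruitment: if "more than 75 therapists are needed to reach the sample size of *N* = 900 patients, additional therapists will be randomized". It does not mention practices.

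**Other sections.** Cluster Definition defines clusters as practices and says "More than one therapist per practice is allowed to participate in the study". Recruitment, Intervention, and Potential Problems and Solutions all describe allocation by practice, and the last repeats the joint rule. Sample Size and Power Calculation plans "25 psychotherapy outpatient practice clusters and *n* = 300 patients per study arm", and the Discussion speaks of 75 practices. The Abstract, by contrast, has 75 psychotherapists being randomised.

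**The concern.** The unit of randomisation is an instruction that whoever runs the allocation has to execute. In a single-therapist practice the two statements give the same result. In a joint practice they do not: one sends all colleagues to one arm, the other allocates each person separately. The protocol allows joint practices and gives them their own stratum, so the difference is not hypothetical.

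If colleagues in one practice were allocated separately, a practice could deliver blended therapy and standard CBT side by side. The protocol says the joint rule exists to prevent this. Contamination makes arms more alike, and in a non-inferiority trial that pushes the result towards the claim the trial hopes to make.

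The count has the same mix-up of units. The sample size is built on practices as clusters, but the trigger for adding clusters is written in therapists. Once some practices contribute more than one therapist, 75 therapists means fewer than 75 practices.

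**Working it through.** **1. The plan's own figure.** Inputs from Sample Size and Power Calculation: margin 0.24 SD, one-sided α = 0.025, power 0.80, ICC 0.01, 12 patients per cluster. A true difference of 0 is assumed.

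- Patients per arm without clustering: 2 × (1.960 + 0.842)² / 0.24² = 272.5, rounded up to 273.
- Design effect: 1 + (12 − 1) × 0.01 = 1.11.
- Patients per arm with clustering: 273 × 1.11 = 303.0, or 303.0 / 12 = 25.25 clusters.
- Stated: 300 patients and 25 clusters per arm. This reproduces within rounding. Power at 300 per arm is Φ(0.24 / √(2 × 1.11 / 300) − 1.960) = Φ(0.830) = 0.797.

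So the calculation treats a cluster as 12 patients and labels that cluster a practice. This fits Cluster Definition, where 12 is the target per therapist, only if each practice has one participating therapist.

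**2. The two allocation rules in a two-therapist practice.**

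| Rule applied | P(the two therapists are in different arms) |
|---|---|
| Joint allocation by practice | 0 |
| Individual, simple independent 1:1:1 | 1 − 3 × (1/3)² = 2/3 |
| Individual, both draws in the same block (block size not stated; 3, 6, 9, 12 assumed) | 1.00, 0.80, 0.75, 0.73 |

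For a block of size b, the last row is 1 − (b/3 − 1)/(b − 1).

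**3. What counting in therapists does to the number of practices and to power.** Let q be the share of practices that contribute two therapists, with 12 patients each. The protocol gives no such share, so q is assumed. Patients per arm stay at 300.

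- Practices from 75 therapists: 75 / (1 + q).
- Size-weighted mean cluster size: 12 × (1 + 3q) / (1 + q).
- Design effect: 1 + (size-weighted mean − 1) × 0.01.
- Power: Φ(0.24 / √(2 × design effect / 300) − 1.960).

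| q (assumed) | Practices, total | Practices per arm | Weighted cluster size | Design effect | Power |
|---|---|---|---|---|---|
| 0 | 75 | 25 | 12.0 | 1.110 | 0.797 |
| 0.1 | 68.2 | 22.7 | 14.2 | 1.132 | 0.789 |
| 0.2 | 62.5 | 20.8 | 16.0 | 1.150 | 0.783 |
| 0.3 | 57.7 | 19.2 | 17.5 | 1.165 | 0.777 |

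With the ICC of 0.01 applied at practice level, the loss is about two percentage points at most over this range.

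**The case against.** The strongest reply is that the intention is clear. The joint rule is stated twice, without exception for late entrants. Recruitment and Intervention allocate practices, the billing feature for blended services is assigned to the practice, and stratifying by number of therapists makes sense only if the practice is the unit. On this view the individual-level phrase is loose wording, perhaps meaning that units are drawn one at a time. This is the most plausible reading, and it is why the fix is small. It does not remove the contradiction: the sentence is unqualified, the Abstract also speaks of randomising psychotherapists, and the sentence on additions again names therapists.

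A reader might infer that late or replacement therapists are to be randomised individually, so that a colleague joining an allocated practice would land in another arm two times in three. The document does not say this. The individual-level sentence is general and mentions neither late nor replacement therapists; the following sentence on additions does not say how a therapist in an already allocated practice would be handled. Cluster Definition speaks of opening clusters throughout recruitment, which fits adding new practices. Re-randomising a colleague is the reading least consistent with the joint rule, so 2/3 is a conditional figure and not a property of the plan. That the article has no separate rule for late joiners is detail the full protocol may hold.

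A reader might also infer that the trial stops at 75 therapists and so falls short of its planned practices. It does not: more are added if needed to reach 900 patients. The shortfall in practices matters only through larger clusters, and that effect is small.

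**Conclusion.** The point stands as an internal contradiction. The section on randomisation gives two units that cannot both be applied in a joint practice, and it counts 75 therapists where the sample size section and the Discussion plan 25 practices per arm, 75 in all.

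What is at stake is allocation integrity, not power. A split practice arises with probability 2/3 only if the individual-level sentence is applied to two colleagues under simple independent 1:1:1 allocation; under the joint rule it cannot arise. The power effect of the count mix-up is about 0.80 falling to 0.78, and rests on the protocol's ICC of 0.01, a true difference of 0, 12 patients per therapist, and an assumed 20–30% of practices contributing two therapists.

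**What to change.** In Randomization, Allocation, and Masking:

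- Delete or correct the individual-level phrase, and state that the practice is the only unit randomised, 1:1:1.
- State that a practice's stratum (one therapist or more than one) is fixed when it is randomised.
- State that the trial is enlarged by randomising additional practices, and that no practice is ever split across arms.
- Restate the count and the trigger for additions in practices: 25 per arm, 75 in total. Align the Abstract with this.

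Whether a colleague who enrols later takes the practice's existing arm or is not admitted is a choice for the trial team. Taking the existing arm follows from the joint rule but means the arm may be known before the colleague enrols; not admitting loses a few willing therapists. Either keeps practices whole.

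The cost is a few sentences and no change to the sample size. It is best done while clusters are still being opened, because a practice already split between arms cannot be repaired in the analysis.

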### Intervention

PSYCHOnlineTHERAPY provides the mean of combining standard psychotherapeutic care as described below (see control condition) with Internet- and mobile-based intervention modules. Based on psychotherapy practice study arm allocation patients receive either PSYCHOnlineTHERAPY_fix/flex_ or CBT_standard_.

All patients with a diagnosed depressive or anxiety disorder as defined in the inclusion criteria can take part in a psychotherapy reimbursed based on the PNP contract. In adult psychotherapy, acute care of up to 10 h is reimbursed (as of October 20th 2020) with 120 €. Initial treatment of a maximum of 20 h is reimbursed at 115 €. Further treatment is possible with up to 30 sessions (105 €). The first max. 16 psychotherapy sessions are defined as trial intervention of PSYCHOnlineTHERAPY. Thereby, the trial definition of 16 sessions follows both trial feasibility considerations as well as psychotherapy dose-response findings, with 4–24 sessions being reported as optimal dose in routine treatment settings (44). Patients of all three trial arms will receive standard PNP-based psychotherapy following the first 16 sessions in case of still existing need of psychotherapy as defined by the therapist. As only psychotherapists with a CBT background are eligible for this trial, PNP-based psychotherapy will be CBT-based.

#### Control Group—CBT_standard_

Patients enrolled in PSYCHOnlineTHERAPY and allocated to the control group will receive standard psychotherapy as described before, following the obligatory diagnostic process in the first few sessions (Table 1). Thereby, therapy follows standard care without a predefined treatment protocol. Details of the psychotherapy provided will be assessed via therapy documentation sheets in order to provide a *post-hoc* description of standard psychotherapy as provided in standard care.

**Table 1 T1:** PSYCHOnlineTHERAPYfix/flex vs. CBTstandard.

**PSYCHOnlineTHERAPY_**fix**_**	**PSYCHOnlineTHERAPY_**flex**_**	**CBT_**standard**_**
on-site diagnostics, indication for psychotherapy and evaluation of suitability for PSYCHOnlineTHERAPY as well as informed consent		
max. 16 sessions in a fixed order alternating an online-intervention module followed by a standard psychotherapy session	max. 16 online or standard sessions, amount and order of online and standard sessions as defined by their therapists	max. 16 standard psychotherapy sessions
end of PSYCHOnlineTHERAPY (standard PNP-based psychotherapy following the first 16 sessions in case of still existing need of psychotherapy as defined by the therapist)		

#### Intervention Groups – PSYCHOnlineTHERAPY

Patients allocated to the intervention group will receive PNP-based psychotherapy as aforementioned, combined with Internet- and mobile-based modules (Table 1).

PSYCHOnlineTHERAPY was developed by the Department of Clinical Psychology and Psychotherapy, Ulm University. The content has been specifically tailored to the needs of psychotherapy outpatients as well as their psychotherapists based on experience from a multitude of prior Internet- and mobile-based intervention development processes and clinical trials [e.g., (29, 45–47)]. Patient and psychotherapist feedback on former versions of the intervention modules has been used to further optimize the modules. The overall web-design was revised based on persuasiveness principles (48). Various interactive design elements such as videos, audio files, pictures, and exercises are included in order to optimize user experience and facilitate intervention adherence.

Intervention content consists of seven Internet- and mobile-based modules for depressive disorders, seven for each of the included anxiety disorders, 22 transdiagnostic modules as well as one introductory and one closing module (Table 2) with an estimated proceeding duration of 45–60 min each. They are based on CBT-principles including psychoeducation, many exercises and homework assignments to promote transfer into everyday life. To illustrate therapeutic principles and exercises within the intervention, fictional patients are introduced in the beginning of the intervention and used to illustrate processes, challenges, and possible solutions throughout the intervention modules.

**Table 2 T2:** Intervention content.

**Modules**	**Content**
Introduction	Platform features, presentation of example patients
**Depression modules**	
Psychoeducation	Introduction, symptoms, Lewinsohn's depression model
Lifeline and therapy goals	Drawing lifeline, risk factors, resources, therapy goal setting
Activities	Depression spiral, activity planning
Depression pitfalls	Behavioral patterns, self-observation, problem solving skills
ABC model	Presentation of the model, individual formulation of components
Cognitive restructuring	Beneficial and impeding thoughts, consequences and connection with emotions, restructuring methods
Emotions	Introduction to and cultural rules of emotions, components of emotion
**Anxiety modules**	
Psychoeducation: development of anxiety^*^	Introduction, symptoms, anxiety levels, diathesis-stress model
Psychoeducation: maintenance of anxiety^*^	Vicious circle, individual formulation of initiating and maintaining factors
Dealing with anxiety reactions	Safety seeking and avoidance behavior, perception control, exercises
Anxiety process^*^	Situation exploration, fear hierarchy, worst possible consequences
Motivation	Cost-benefit relation, neglected activities, goal setting
Confrontation^*^	Confrontation therapy, protocol, exposition exercises in sensu and *in vivo*
Pleasant thoughts	Reflection of thoughts, stress reducing thoughts, exercises
Closing module	Resources, goal setting, emergency plan, motivation
**Transdiagnostic modules**	
Mindfulness	Introduction, effects of mindfulness, exercises
Physical activity	Importance, recommendations, assessment, goal setting, everyday activity
Sleep	Healthy sleep, sleep disorders, stimulus control exercises
Social competence training I	Social situations and competence, confident behavior, asserting rights
Social competence training II	Social situations and competence, confident behavior, recognizing emotions, managing relationships
Grief	Grief reaction, secondary losses, rumination, detrimental thoughts
Pain	Understanding pain, activity despite pain, rumination, relaxation
Relaxation	Introduction, relaxation and meditation exercises
Relationship and sexuality	Communication, needs, relaxation, massages
Self-esteem and self-image	Importance of self-esteem and self-image, elevating self-esteem, values
Self-compassion	Importance of self-care, learning self-compassion
Loneliness	Loneliness vs. being alone, dealing with loneliness, building relationships, exercises
Gratitude	Importance of gratitude, learning gratitude
Perfectionism	Illusion of perfection, origin and consequences, tolerate and accept imperfection
Procrastination	Understanding procrastination, connection with Internet, importance of self-regulation, exercises to overcome procrastination
Substance use	Problematic substance use and reflection, distraction, alternative behavior
Stress	Meaning of work, connection between work-related stress and mental illness, problem- and emotion-focused stress management
Social media	Problematic usage, SORCK-Model, alternative activities, strategies of self-regulation
Somatoform symptoms	Understanding health and illness, connection between stress and physical complaints, ABC model, physical activity
Acceptance	Short-term problem-solving strategies, primary vs. secondary suffering, learning acceptance
Values and goals	Definition of individual values, goal setting, beneficial key assumptions
Stigma	Diagnostic label, self- and public-stigma, sharing diagnosis

* *Individual modules for agoraphobia, generalized anxiety disorder, panic disorder, social phobia, and specific phobia*.

The intervention is available to participants on eSano, an open source e-health platform developed by Ulm University for providing a technological infrastructure to create and deliver a multitude of IMIs. The platform is divided into three sub-platforms. Intervention content is designed and created in the web-based Content Management System. The intervention is then made available to participants in the cross-platform patient application (web-based, Android, iOS). During the intervention therapeutical guidance can be provided using the web-based e-coach platform. Communication and data transfer between all sub-platforms are end-to-end encrypted with TLS. All eSano systems are located in an isolated network environment, whose interfaces to adjacent networks are regulated by firewalls with appropriate rules. These rules are defined to allow a necessary minimum of communication. The platforms are developed oriented on the requirements of the German Medical Devices Act and the Medical Device Regulation (MDR). Thus, the software development and validation process takes into account the IEC 62304 (safety class B), the GAMP5 (category 4), the General Principles of Software Validation of the FDA as well as the Pharmaceutical Inspection Cooperation Scheme (PIC/S) 11-3.

PSYCHOnlineTHERAPY modules can be used by therapists and patients in varying forms, operationalized in the present study in two versions:

PSYCHOnlineTHERAPY_fix_: Patients receive alternating online-intervention modules and standard psychotherapy sessions with a fixed ratio of max. eight online and eight standard sessions. Thereby, therapists are free to choose amongst the available intervention modules and in their decision of module order.

PSYCHOnlineTHERAPY_flex_: Patients receive a flexible number of up to 16 online or standard sessions as defined by their therapist. Thereby, therapists are free to choose amongst the available intervention modules and in their decision of module order as well as frequency.

Both conditions, PSYCHOnlineTHERAPY_fix_ and _−flex_ do not comprise therapeutic guidance in an Internet-based self-help intervention sense of way (31). Therapists are requested to check patients online-session activities prior to the next online or standard session. This process is reimbursed at 20 € within the PNP contract per therapists' check of patients' online-session activities. It is possible to provide a written feedback within the eSano platform, however, the PNP billing code is not designed for this therapeutic intervention guidance, but rather a quality assurance check of estimated 5–15 min time per patient and online session.

